## Abstract

**Background:**

Infections occur in 30% of stroke patients and are associated with unfavorable outcomes. Preventive antibiotic therapy lowers the infection rate after stroke, but the effect of preventive antibiotic treatment on functional outcome in patients with stroke is unknown. The PASS is a multicenter, prospective, phase three, randomized, open-label, blinded end-point (PROBE) trial of preventive antibiotic therapy in acute stroke. Patients are randomly assigned to either ceftriaxone at a dose of 2 g, given every 24 h intravenously for 4 days, in addition to standard stroke-unit care, or standard stroke-unit care without preventive antibiotic therapy. The aim of this study is to assess whether preventive antibiotic treatment improves functional outcome at 3 months by preventing infections. This paper presents in detail the statistical analysis plan (SAP) of the Preventive Antibiotics in Stroke Study (PASS) and was submitted while the investigators were still blinded for all outcomes.

**Results:**

The primary outcome is the score on the modified Rankin Scale (mRS), assessed by ordinal logistic regression analysis according to a proportional odds model. Secondary analysis of the primary outcome is the score on the mRS dichotomized as a favorable outcome (mRS 0 to 2) versus unfavorable outcome (mRS 3 to 6). Secondary outcome measures are death rate at discharge and 3 months, infection rate during hospital admission, length of hospital admission, volume of post-stroke care, use of antibiotics during hospital stay, quality-adjusted life years and costs. Complications of treatment, serious adverse events (SAEs) and suspected unexpected serious adverse reactions (SUSARs) are reported as safety outcomes.

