### Summary study protocol

PASS is a multicenter prospective, randomized, phase III, open-label, blinded end-point superiority trial (PROBE) of standard care with preventive ceftriaxone treatment compared to standard care without preventive ceftriaxone. Adult patients with stroke (both ischemic and hemorrhagic), a score ≥1 on the National Institutes of Health Stroke Scale (NIHSS) and stroke onset within 24 hours were included
[8]. Patients were excluded in case of infection at admission, use of antibiotics within 24 hours before admission, previous hypersensitivity or anaphylaxis to cephalosporins or penicillin, subarachnoid hemorrhage, pregnancy or when death seemed imminent. Patients were randomly assigned to either ceftriaxone at a dose of 2 g, given every 24 h intravenously for 4 days, in addition to stroke-unit care, or standard stroke-unit care without preventive antibiotic therapy. Randomization was performed through ALEA (online software for randomized trials;
https://nl.tenalea.net/amc/ALEA/Login.aspx) and is based on a uniform distribution; weight of the arms is equal (1:1). Randomization is stratified according to study center (academic hospital, large non-academic hospital, or small non-academic hospital) and stroke severity (score on NIHSS 1 to 9 or >9) and performed by using random blocks with a maximum block size of 6; blocks of 2, 4 and 6 are made per stratum combination

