[9]. The study has a PROBE design, which implies that blinding is lost, but only as to treatment. Patient and physician were aware of treatment allocation; however, the assessors of outcome were not. Data were collected on admission, during hospital stay, and at 3 months by standardized case record forms. The primary outcome is functional outcome at 3 months follow-up, as assessed on the mRS during a structured telephone interview by a trained assessor blinded for treatment allocation. Secondary outcomes are death rate at discharge and at 3 months, infection rate during hospital admission, length of hospital admission, volume of post-stroke care, use of antibiotics during hospital stay, quality adjusted life years (QALYs) and costs. Safety outcomes are complications of treatment, Serious adverse events (SAEs) and suspected unexpected serious adverse reactions (SUSARs). In the initial trial protocol, we presented a binary logistic regression analysis on the dichotomized mRS (0 to 2 versus 3 to 6) as primary outcome, requiring a sample size of 3,200 patients, and a proportional odds model in a secondary analysis of the primary end point
[9]. Blinded for any of the outcomes, we have changed the primary analysis in PASS from a binary logistic to an ordinal logistic regression on the original mRS, enhancing statistical power. The adapted power analysis showed that with identical assumptions on the clinical effect, using a 0.05 two-sided significance level and 80% study power, 2,550 patients were needed
[9]. The analysis of dichotomized mRS data will now be the secondary analysis of the primary end point.

On 23 March 2014, all patients were included and the last follow-up is expected in June 2014. For the complete study protocol and update, we refer to previous publications
[6, 7].

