### Baseline characteristics

Baseline characteristics of all patients will be outlined per treatment allocation in a baseline table describing the following variables: age, sex, medical history (atrial fibrillation/flutter, stroke, hypercholesterolemia, hypertension, myocardial infarction, cardiac valve insufficiency/stenosis/replacement, peripheral vascular disease, obstructive pulmonary disease, and immunocompromised), current smoking, specific medication (anticoagulants, antiplatelet, statin, ACE inhibitor, ß-blocker, and proton pump inhibitor) prior to stroke, disability prior to stroke on mRS, stroke severity on NIHSS, performance of a screening test for swallowing function, dysphagia, acute treatment (IV thrombolysis and anticoagulant antagonist therapy) and diagnosis at discharge (infarct, haemorrhage, TIA, or other). Outline of the table is displayed in the ‘Outline of figures and tables’ section (Table 
3). All variables will be presented categorized by treatment arm. Dichotomous variables will be displayed in percentage with the number of patients divided by the total number of evaluated patients. Continuous variables will be reported as means with standard deviations when normally distributed and in medians with interquartile ranges when they do not meet the criterion of being normally distributed, as assessed by the Kolmogorov-Smirnov test. For continuous variables, the number of patients evaluated will be presented in a footnote of Table 
3.

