### Analysis of primary outcome

An ordinal regression model on the total range of the mRS will be performed as the first analysis of primary outcome, under the assumption of proportional odds
[7]. The distribution of primary outcome (for example, functional outcome on the mRS) in both treatment groups will be expressed in a histogram (Figure 
4). Both adjusted and unadjusted analyses will be performed and reported. In clinical trials, adjusting for prognostic covariates improves statistical power, can correct for imbalances in baseline prognostic variables and can reduce variability in data
[17, 18]. The choice of prognostic covariates is mostly based on imbalances across treatment groups, prognostic factors that are related to the primary outcome, or a combination of both
[17]. As the investigators are blinded for all outcome data until the statistical analysis plan is accepted for publication, we chose to use the most important prognostic factors for outcome after stroke: age, stroke severity on the NIHSS, history of stroke, history of diabetes, prior disability as defined on mRS, and stroke type
[19]. Stratification of randomization was performed according to both study center and stroke severity, so we will also include study center as a covariate. The second analysis of the primary endpoint, that is, the dichotomized score on the mRS (for example, favorable versus unfavorable, mRS 0 to 2 versus mRS 3 to 6), will be expressed as OR with 95% confidence intervals (CI; Table 
4). Results of the dichotomized approach will be compared to the results of the primary analysis of primary outcome.

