### Subgroup analysis of primary and secondary outcomes

We will perform the following sub-group analyses for the primary outcome: stroke type (infarction or hemorrhage), stroke severity (NIHSS 1 to 9 or NIHSS 10 to 30), time between stroke symptoms and start of the antibiotic treatment (0 to 12 h versus 12 to 24 h) and age. For the subgroup analysis of primary analysis of primary outcome, the single OR from the proportional odds model will be calculated for each subgroup separately. For the subgroup analysis of secondary analysis of primary outcome, we will tabulate the results and analyze them using the chi-squared test and presented as OR and 95% CI ((Table 
7: subgroup analysis of primary outcome). In addition to these predefined subgroup analyses, we will perform a larger set of exploratory additional analyses. For secondary outcomes, we will perform all the previous mentioned subgroup analyses (stroke type, severity, time to treatment, and age). In addition we will perform analysis on presence of a swallowing disorder, respiratory tract infections, and a urinary catheter.

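### The dichotomized analysis uses mRS 0 to 2 as favorable for every patient although pre-stroke disability is not restricted, so its crude OR and the chi-squared subgroup results are modestly attenuated (minor)

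*SAP article*

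**What the plan says.** The Abstract of the SAP article (Results) defines the dichotomized endpoint as "the score on the mRS dichotomized as a favorable outcome (mRS 0 to 2) versus unfavorable outcome (mRS 3 to 6"). Its status is given under Summary study protocol: "The analysis of dichotomized mRS data will now be the secondary analysis of the primary end point". Analysis of primary outcome adds: "Results of the dichotomized approach will be compared to the results of the primary analysis of primary outcome".

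On who can enter, Summary study protocol gives "Adult patients with stroke (both ischemic and hemorrhagic), a score ≥1 on the National Institutes of Health Stroke Scale (NIHSS"), with onset within 24 hours. The exclusions, which begin "Patients were excluded in case of infection at admission, use of antibiotics within 24 hours before admission", contain nothing on prior disability. The list of eligibility violations in Table 1 contains nothing on it either, so the two places agree.

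The plan nevertheless expects prior disability to vary. Baseline characteristics and Table 3 include "disability prior to stroke on mRS", and Analysis of primary outcome lists it among the prognostic covariates, with adjusted and unadjusted results both to be reported. That statement follows the ordinal model. The dichotomized analysis comes later in the same section, only as an OR with a 95% CI, and Table 4 has a single OR column that is not labeled adjusted or unadjusted.

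For subgroups on the dichotomized outcome, Subgroup analysis of primary and secondary outcomes says "we will tabulate the results and analyze them using the chi-squared test", with an OR and CI. No adjustment is named there. Every block of Table 7 is headed by favorable outcome at mRS 0 to 2.

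**The concern.** A patient who lived at mRS 3, 4 or 5 before the stroke is, for practical purposes, in the unfavorable category from the day of entry. Treatment may move such a patient between 3 and 6, and the ordinal analysis can register that, but the 0 to 2 cut cannot. These patients still count in each denominator, so both arms' favorable rates shrink by the same factor and the crude OR moves toward 1.

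Two uses of the dichotomized result are touched. The plan will set it beside the ordinal result, and attenuation of one could be misread as disagreement between them. The subgroup ORs will also be read against one another. If prior disability is more common at one level of a subgroup factor than at another (plausible for age, but an assumption), a uniform effect would show as slightly unequal ORs.

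**Working it through.** **The plan's own figures.** The article gives 3,200 patients for the original dichotomized analysis and 2,550 for the ordinal one, at two-sided 0.05 and 80% power. It gives no favorable rates, no effect size and no share of patients with pre-stroke mRS 3 to 5, so neither figure can be reproduced. Working backwards with a two-proportion test, 3,200 patients give 80% power for a difference of 4.8 to 4.9 percentage points (OR about 1.22 to 1.23) at assumed control rates of 0.40 to 0.60.

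**Inputs.** From the article: 1:1 allocation, two-sided 0.05, 2,550 patients, 5% lost or incomplete. So 2,550 × 0.95 = 2,422, or n = 1,211 per arm. Assumed: control favorable rate p0 = 0.60 and OR 1.25 among patients able to reach mRS 0 to 2, and a share d with pre-stroke mRS 3 to 5 and no chance of reaching it.

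**Formulas.**
- Treated rate: odds 1.25 × 0.60/0.40 = 1.875, so p1 = 1.875/2.875 = 0.652.
- All patients: a = (1 − d)p0, b = (1 − d)p1, crude OR = [b/(1 − b)] / [a/(1 − a)].
- Power: Φ{ [ (b − a) − 1.96·√(2·p̄(1 − p̄)/n) ] / √( [a(1 − a) + b(1 − b)]/n ) }, with p̄ = (a + b)/2.
- Restricted to pre-stroke mRS 0 to 2: the same power formula with p0, p1 and n(1 − d).

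**Worked case, d = 0.10.** a = 0.540, b = 0.587. OR = (0.587/0.413)/(0.540/0.460) = 1.21. For power: difference 0.0470, null term 1.96 × 0.02016 = 0.0395, denominator 0.0201, so z = 0.37 and power = 64.4%. Restricted analysis: 71.2%.

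| Share d | Crude OR | Power, all patients | Power, pre-stroke mRS 0 to 2 |
|---|---|---|---|
| 0% | 1.25 | 75.6% | 75.6% |
| 5% | 1.23 | 70.0% | 73.5% |
| 10% | 1.21 | 64.4% | 71.2% |
| 15% | 1.20 | 59.0% | 68.7% |

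**Second set of assumptions.** With p0 = 0.50, the effect that 3,200 patients detect at 80% power (OR 1.219) and N = 2,550, shares of 5, 10 and 15% give crude ORs of 1.207, 1.196 and 1.186. Power is 66.0, 61.4 and 56.9%, against 68.3, 66.0 and 63.5% when restricted. The pattern is the same and the gain smaller.

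**Size against precision.** At d = 0.10 in the first set, the log OR falls from 0.223 to 0.191, a shift of 0.032. The standard error of the log OR is about 0.082, so the shift is 0.39 standard errors, inside a 95% CI of about 1.03 to 1.42.

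**What adjustment does.** An expected-data logistic regression with N = 2,550 used an assumed pre-stroke mRS distribution of 65, 15, 10, 7, 2.5 and 0.5% for scores 0 to 5. Control favorable rates were 58, 42, 30, 0, 0 and 0%, and the conditional OR was 1.219. The unadjusted OR is 1.185 (z = 2.15). Adding pre-stroke mRS as a linear term returns 1.219 (z = 2.32). Restricting to 0 to 2 without adjustment gives 1.210 (z = 2.27).

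**Subgroups.** A uniform OR of 1.25 appears as 1.23 in a level with 3% pre-disabled (65% favorable among able controls) and as 1.18 in a level with 30% pre-disabled (50% favorable). The log-OR gap is 0.210 − 0.167 = 0.043. For two equal halves of the trial, the standard error of the difference in log OR is about 2 × 0.082 = 0.164, so the artificial gap is about 0.26 standard errors.

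**The case against.** The strongest reply is that nothing here is an error. The proportion at mRS 0 to 2 among all randomized patients is a well-defined intention-to-treat quantity, validly estimated and unbiased when treatment does nothing. Any fixed cut includes patients unlikely to cross it. The plan also made the ordinal analysis primary, and that analysis keeps the information from patients who move between 3 and 6. The subgroup section gives the ordinal OR per subgroup first. Prior mRS is already a listed covariate, and the paragraph promising adjusted results is in the same section as the dichotomized analysis. If the design rates described unselected stroke patients, planned power already allowed for the dilution; the article does not say.

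Most of this stands. A reader might infer that the dichotomized result is biased, that it threatens the primary conclusion, or that patients with pre-stroke mRS 3 to 5 should be dropped from it. The documents support none of these. There is attenuation, not false effect; the primary analysis does not use the cut; and replacing the all-patient set would change the estimand and depart from the plan's intention-to-treat principle. A visible conflict between the two analyses is also unlikely, because a crude ordinal OR that omits prior mRS is pulled toward 1 as well.

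What the reply does not cover is the wording. The section does not say that adjustment extends to the dichotomized OR, Table 4 does not show which OR it holds, and for dichotomized subgroups only the chi-squared test with an OR and CI is specified.

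**Conclusion.** The point holds as a minor one. One cut is applied to a population with no limit on pre-stroke disability, so the crude dichotomized OR and the chi-squared subgroup results understate the effect among patients able to reach mRS 0 to 2, and they lose some power. Under the first set of assumptions the crude OR moves from 1.25 to between 1.23 and 1.20 for shares of 5 to 15%. Power is 3.5 to 9.7 points below that of an analysis in patients with pre-stroke mRS 0 to 2 (73.5 − 70.0 and 68.7 − 59.0).

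These sizes rest on an assumed favorable rate, an assumed effect, an assumed pre-disabled share and a zero chance of a favorable outcome in that share; a small non-zero chance would reduce them. Distortion between subgroups is real in direction, but even in the extreme example it is well below what the trial could resolve.

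**What to change.** Keep the all-patient intention-to-treat dichotomized result as planned. Then:

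- In Analysis of primary outcome and in the subgroup section, state that the dichotomized OR, including each subgroup OR, is also estimated by logistic regression adjusted for pre-stroke mRS and the other prespecified covariates. Label the OR columns of Tables 4 and 7 as adjusted or unadjusted.
- State how pre-stroke mRS enters the model. If it enters as categories and a level has no favorable outcomes, that level has no finite coefficient.
- Add one supporting row, chosen in advance: either patients with recorded pre-stroke mRS 0 to 2, a set defined at baseline so that the randomized comparison is kept, or all patients with favorable defined as mRS 0 to 2 or no worse than the pre-stroke score. State what is done when the pre-stroke score is missing.

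The cost is a few sentences and an extra row per table. No new data are needed, since pre-stroke mRS is already recorded. The restricted row describes only patients without major prior disability and uses fewer of them, which is why it should support the all-patient result and not replace it. The ordinal primary analysis is unchanged.

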**Conclusions:**

The data from PASS will establish whether preventive antibiotic therapy in acute stroke improves functional outcome by preventing infection and will be analyzed according to this pre-specified SAP.

**Trial registration:**

Current controlled trials;
ISRCTN66140176. Date of registration: 6 April 2010.

## Update

### Introduction

Stroke is a leading cause of death worldwide
[1]. Infections occur in 30% of stroke patients and are associated with unfavorable outcomes
[2, 3]. Preventive antibiotic therapy lowers infection rate in patients after stroke, but the effect of preventive antibiotic treatment on functional outcome after stroke has not yet been investigated
[4, 5]. The Preventive Antibiotics in Stroke Study (PASS) is a phase three randomized clinical trial investigating whether the preventive use of the antibiotic ceftriaxone improves functional outcome in acute stroke patients by preventing infections. We previously published the trial protocol and an update of this protocol; we now present the statistical analysis plan (SAP)
[6, 7]. This SAP was drafted without knowledge of any of the outcomes by the investigators and randomization code will not be broken before acceptance of the current paper for publication.

### Summary study protocol

PASS is a multicenter prospective, randomized, phase III, open-label, blinded end-point superiority trial (PROBE) of standard care with preventive ceftriaxone treatment compared to standard care without preventive ceftriaxone. Adult patients with stroke (both ischemic and hemorrhagic), a score ≥1 on the National Institutes of Health Stroke Scale (NIHSS) and stroke onset within 24 hours were included
[8]. Patients were excluded in case of infection at admission, use of antibiotics within 24 hours before admission, previous hypersensitivity or anaphylaxis to cephalosporins or penicillin, subarachnoid hemorrhage, pregnancy or when death seemed imminent. Patients were randomly assigned to either ceftriaxone at a dose of 2 g, given every 24 h intravenously for 4 days, in addition to stroke-unit care, or standard stroke-unit care without preventive antibiotic therapy. Randomization was performed through ALEA (online software for randomized trials;
https://nl.tenalea.net/amc/ALEA/Login.aspx) and is based on a uniform distribution; weight of the arms is equal (1:1). Randomization is stratified according to study center (academic hospital, large non-academic hospital, or small non-academic hospital) and stroke severity (score on NIHSS 1 to 9 or >9) and performed by using random blocks with a maximum block size of 6; blocks of 2, 4 and 6 are made per stratum combination
[9]. The study has a PROBE design, which implies that blinding is lost, but only as to treatment. Patient and physician were aware of treatment allocation; however, the assessors of outcome were not. Data were collected on admission, during hospital stay, and at 3 months by standardized case record forms. The primary outcome is functional outcome at 3 months follow-up, as assessed on the mRS during a structured telephone interview by a trained assessor blinded for treatment allocation. Secondary outcomes are death rate at discharge and at 3 months, infection rate during hospital admission, length of hospital admission, volume of post-stroke care, use of antibiotics during hospital stay, quality adjusted life years (QALYs) and costs. Safety outcomes are complications of treatment, Serious adverse events (SAEs) and suspected unexpected serious adverse reactions (SUSARs). In the initial trial protocol, we presented a binary logistic regression analysis on the dichotomized mRS (0 to 2 versus 3 to 6) as primary outcome, requiring a sample size of 3,200 patients, and a proportional odds model in a secondary analysis of the primary end point
[9]. Blinded for any of the outcomes, we have changed the primary analysis in PASS from a binary logistic to an ordinal logistic regression on the original mRS, enhancing statistical power. The adapted power analysis showed that with identical assumptions on the clinical effect, using a 0.05 two-sided significance level and 80% study power, 2,550 patients were needed
[9]. The analysis of dichotomized mRS data will now be the secondary analysis of the primary end point.

On 23 March 2014, all patients were included and the last follow-up is expected in June 2014. For the complete study protocol and update, we refer to previous publications
[6, 7].

### Protocol developments

PASS is registered at current controlled trials (
http://www.controlled-trials.com; ISRCTN: 66140176; date of registration: 6 April 2010). The medical-ethical board of the Academic Medical Center, Amsterdam, approved the protocol on 5 May 2010, and 29 Dutch participating centers were added in the course of the study. Due to the change in primary analysis of primary outcome from a binary logistic approach to an ordinal logistic regression analysis and an expected rate of patients lost to follow-up and/or patients with incomplete data of 5%, the total sample size was reduced from 3,200 patients to 2,550 patients in 2014
[7]. Importantly, no changes were made regarding the primary outcome measurement (that is, the assumed size of the effect on the mRS). This update of the protocol was recently published in this journal
[7].

